### Statistical analysis

The IBM SPSS 20.0 (IBM Corp., Armonk, NY, USA) statistics program will be used for all analysis. Categorical variables will be expressed as delivery rate when comparing baseline features between the SCUBA™ and COMPLETE-SE™ stent groups and for categorical variables, comparisons between groups will use the chi-square or Fisher’s exact test. Continuous variables will be expressed as mean ± standard deviation, and for continuous variables, comparisons between groups will use the Student’s *t* test. The primary and secondary end points will be analyzed using both intention-to-treat analysis (all subjects assigned to a treatment group) and per protocol analysis (only subjects who completed the treatment protocol). Noninferiority will be considered proven if conclusions drawn from the intention-to-treat and per protocol analyses are consistent. Balloon-expandable stent patency will be judged as noninferior to that of the self-expandable stent when the lower limit of the 95 % CI of the difference between the proportions of patent patients at 1 year in both groups is higher than -δ = −10 % At the end of the 12 months, cumulative restenosis rates will be calculated. For a secondary end point, we will summarize with descriptive statistics and compare between treatment groups using the Student’s *t* test, chi-square test, or Fisher’s exact test. Also, clinical outcomes such as revascularization of the target vessel, death, major cardiovascular events including myocardial infarction and cerebral infarction, and limb salvage rates will be analyzed using Kaplan-Meier survival estimates and a comparison of the groups will be performed using the log-rank test. A *P* value <0.05 will be considered to be statistically significant. In order to evaluate the risk factors for recurrence, defined as restenosis or total occlusion, univariate and multivariate logistic regression analysis will be performed. The present research has concluded that there will be a very low chance of missing data to cause bias, and therefore, missing data for the major end points will be excluded from the analysis data.

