### Study population

Patients at least 20 years of age who have moderate or severe intermittent claudication or critical limb ischemia (CLI), Rutherford score of 2 to 6, except for any patient who has undergone or plans to have a major amputation) will be screened for study enrollment. Prior to inclusion, morphological examinations such as computed tomography (CT) and magnetic resonance imaging (MRI) are not necessarily needed. However, we will usually examine the CT angiography prior to the intervention. A patient will be enrolled if they meet all of the inclusion criteria and have none of the exclusion criteria. Inclusion criteria consist of clinical and anatomical criteria.

The clinical inclusion criteria are as indicated below: Symptomatic peripheral artery disease with moderate to severe claudication (Rutherford score of 2 to 3) Chronic CLI with resting ischemic pain (Rutherford score of 4) Chronic CLI with ischemic ulcers (Rutherford score of 5 to 6) Patients must provide written informed consent

The anatomical inclusion criteria are as indicated below: Stenosis of more than 50 % Occlusion of the ipsilateral iliac artery Patent (≤50 % stenosis) ipsilateral femoropopliteal artery, or concomitantly treatable ipsilateral femoropopliteal lesions (≤30 % residual stenosis), and at least one patent (less than 50 % stenosis) tibioperoneal run-off vessel. We will not exclude patients who have undergone femoral endareterectomy. If inflow and outflow disease can be treated (except by bypass surgery), we will enroll these patients

Exclusion criteria include the following:Failure to provide written informed consentA history of major bleeding within the prior 2 monthsKnown hypersensitivity or contraindication to any of the following medications: heparin, aspirin, clopidogrel, cilostazol, or contrast agentAcute limb ischemiaPrevious bypass surgery or stenting of the ipsilateral iliac arteryUntreated inflow disease of the distal aorta (>50 % stenosis or occlusion)Patients who have undergone major amputation (amputation of above the ankle) or major amputation is planned or requiredPatients with a life expectancy of less than 1 year due to comorbidities

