#### Sample size calculation

Although patency definitions varied across trials, 1-year patency rates in aortoiliac lesions were approximately 90 % on average from previous studies including CRISP-US and MELODIE [22, 23]. In the case of the SCUBA™ stent, the 9-month patency rate for the SCUBA™ stent was 99.2 % in the ACTIVE study - a prospective, multicenter, single-arm study that defines the midterm efficacy of a next-generation cobalt-chromium iliac stent for the treatment of de novo and restenotic lesions in iliac arteries [25]. However, a different definition - a ratio of <2.4 between the duplex peak systolic velocity in the treated vessel segment and the reference systolic velocity - was used, unlike the more common definition. There are limited data on the 1-year primary patency rate of the SCUBA™ stent. Based on the MELODIE trial [23], and the European multicenter iliac stent trial [26], the 1-year primary patency of the SCUBA™ stent was estimated to be 88 %, and the COMPLETE-SE™ stent was estimated to be 94.7 % in the CRISP-US trial. Therefore, the self-expandable COMPLETE-SE™ stent group will be the control group, and the balloon-expandable SCUBA™ stent group will be the experimental group.

Patency rate will be defined as absence of occlusion and absence of >50 % stenosis in the treated segment by quantitative coronary angiography (QCA) or if invasive angiography is not performed, PSVR ≤2.5 when evaluated with duplex ultrasound. On the basis of previous studies [22, 23], we hypothesize that the expected patency rate after stent deployment at 1 year would be 90 % for the self-expandable stent group, and 88 % for the balloon-expandable stent group, respectively. The predetermined noninferiority margin δ is a 10 % difference between treatment groups. There was clinical consensus that this noninferiority margin would be acceptable if safety is maintained and patients are treated more easily, regardless of stent classification. The power analysis is based on a noninferiority principle. The statistical significance level is 2.5 % at one side, the power of the test is set as 80 %, and the randomization ratio is set as 1:1. The test for proportion and the chi-square method will be used. Using standard sample size formula, it was calculated that 120 patients per group are needed for a total of 288 patients, after accounting for a 20 % dropout rate.

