## Discussion

A primary endovascular approach may be attempted in all patients with peripheral artery obstructive disease including iliac lesions. In performing endovascular repair for iliac artery lesion, different strategies and types of stents are needed, as described above. There is no general consensus on which stents, balloon-expandable or self-expandable stents are the most appropriate for specific lesion of the iliac artery.

The factors associated with patency after stent implantation in iliac lesion have been known to be various: patient characteristics, lesion characteristics, and so on. Recently, various self-expandable nitinol stents have been manufactured with improved radial force, reduced stent deformity or fracture, and convenient deployment systems. Currently, self-expandable nitinol stents have been the most widely used.

The next-generation balloon-expandable stent has been developed. The first Assurant® balloon-expandable stent system (Medtronic, Inc., Santa Rosa, CA, USA) made from a cobalt-chromium alloy is to be approved by the Food and Drug Administration (FDA) for the treatment of narrowed iliac arteries. The mechanical properties of the cobalt-chromium alloy allow the device to have thinner struts and a low profile, which provide increased flexibility while maintaining radial strength and fluoroscopic visibility [27]. In the ACTIVE study [25], the balloon-expandable Assurant® cobalt-chromium iliac stent demonstrated primary patency at 9 months of 99.2 %, device and lesion success were each 97.5 % (155/159), and the procedural success was 96.7 %.

In real-world clinical practice, physicians tend to deploy self-expanding stents in the mid-iliac area due to severe angulation and tortuosity for fear of iliac artery injury including extravasation, dissection, or rupture following high-pressure balloon inflation with longer balloon-expandable stents. It will be of interest to see the safety rate of balloon-expandable stents in the tortuous mid-iliac artery.

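### The primary noninferiority interval is valid but unadjusted; prespecified adjustment for lesion type and limb status would be a modest, low-cost gain in precision

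*Protocol article*

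**What the plan says.** All references are to the protocol article.

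- **Decision rule (Statistical analysis).** The balloon-expandable stent is noninferior if "the lower limit of the 95 % CI of the difference between the proportions of patent patients at 1 year in both groups" lies above -10 %. The intention-to-treat and per-protocol conclusions must agree.
- **Design-stage test (Sample size calculation).** A test for proportions and the chi-square method are named. Neither uses covariates.
- **Prognosis (Discussion).** "The factors associated with patency after stent implantation in iliac lesion have been known to be various: patient characteristics, lesion characteristics". No factor is named as a predictor and no strength is given.
- **What is known at baseline.** Study population defines eligibility by stenosis above 50 %, by "Occlusion of the ipsilateral iliac artery", and by Rutherford class, which separates claudication from critical limb ischemia. Under Randomization and interventions, diagnostic angiography precedes allocation, so lesion type is known by then.
- **Other modelling (Statistical analysis).** To look for risk factors for recurrence, "univariate and multivariate logistic regression analysis will be performed". No covariates are named, and the model is not tied to the treatment comparison.
- **Allocation (Randomization and interventions).** Web-based and 1:1, with no stratification factor mentioned.

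**The concern.** The verdict depends on how wide one confidence interval is. If lesion type or limb status predicts 12-month patency, a crude comparison leaves that explained variation in the standard error. A chance imbalance in occlusions between the groups also passes directly into the estimated difference. A risk difference standardised over prespecified baseline factors targets the same quantity on the same scale as the 10-point margin. In large samples it is at least as precise as the crude difference.

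The trial has little precision to spare, so even a modest gain is worth having if it is cheap. Naming the covariates in advance also closes off a later argument about adjustment if an imbalance appears.

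**Working it through.** **Inputs from the article (Sample size calculation).** Patency "would be 90 % for the self-expandable stent group" and "88 % for the balloon-expandable stent group"; margin 10 points; "The statistical significance level is 2.5 % at one side"; power 80 %; 120 per group and 288 in total after 20 % dropout.

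**1. The plan's own figure.** The unpooled variance term is 0.90×0.10 + 0.88×0.12 = 0.1956. The distance to the margin is 0.10 - 0.02 = 0.08.

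n per group = 0.1956 × (1.960 + 0.842)² / 0.08² = 240.

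The stated 120 per group is not reproduced. The total of 288 equals 2×120×1.2, so 240 was used as the total when the inputs require it in each group.

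**2. Crude analysis at 120 evaluable per group.**
- SE = √(0.1956/120) = 0.0404; half-width = 1.96 × 0.0404 = 7.91 points.
- Power = Φ(0.08/0.0404 - 1.96) = 50.9 %.

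**3. Adjusted analysis.** If baseline factors explain a share R² of the outcome variance, the SE is multiplied by √(1 - R²). R² is an assumption; the article gives no value.

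| Assumed R² | Half-width (points) | Power, 120 per group | n per group for 80 % |
|---|---|---|---|
| 0 | 7.91 | 50.9 % | 240 |
| 0.03 | 7.79 | 52.1 % | 233 |
| 0.05 | 7.71 | 52.9 % | 228 |
| 0.10 | 7.51 | 55.1 % | 216 |

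For scale, with 11 % loss of patency, R² of about 0.025, 0.056 and 0.097 corresponds to a prognostic score with an AUC of about 0.64, 0.70 and 0.75.

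**4. What R² might lesion type supply?** With a share p of occlusions and a patency gap g, R² = p(1-p)g²/(0.90×0.10). Both p and g are assumed.
- p = 0.30, g = 5 points: 0.6 % (power about 51.1 %)
- p = 0.30, g = 13 points: 3.9 %
- p = 0.40, g = 15 points: 6.0 %
- p = 0.40, g = 20 points: 10.7 %

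At 10 % failure overall, the last case means 2 % failure in stenoses and 22 % in occlusions, an odds ratio of about 14. That is an extreme case.

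**5. Simulation check.** 4,000 trials at 120 per group compared the crude difference with a standardised logistic risk difference, using one prognostic and three noise covariates.

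| AUC of the prognostic covariate | Crude power | Adjusted power |
|---|---|---|
| none | 52.9 % | 52.4 % |
| 0.64 | 52.4 % | 53.1 % |
| 0.70 | 50.1 % | 52.4 % |
| 0.75 | 52.1 % | 55.5 % |

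This agrees with step 3, and shows no gain when nothing is prognostic.

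**6. Chance imbalance.** If allocation is not stratified by lesion type and 30 % of lesions are occlusions, the difference in occlusion share between groups has SD √(2×0.30×0.70/120) = 5.9 points. With a 15-point gap, a two-SD imbalance moves the crude estimate by 2 × 0.059 × 15 = 1.8 points.

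**7. Limits.** Expected failures are 120×0.10 + 120×0.12 = 26.4, which restricts the number of covariates. Reaching 80 % power with 120 per group would need R² = 1 - 120/240 = 0.50.

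**The case against.** The strongest reply is that nothing here is wrong. A crude difference in proportions is a valid noninferiority analysis, sits on the scale of the margin, matches the test named for the sample size, and contradicts no other section. An adjusted sensitivity analysis could also stand in an analysis plan that is not shown. The validity point stands in full. The last point stands only in part, because the article does fix the primary rule, and that rule is crude.

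Four stronger readings are tempting and are not supported:

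- **That precision is being given away free.** The gain depends on a prognostic strength the article does not give. Under weak prognosis it is close to zero, and adjustment has costs. Patients are also randomised only after wire passage and a suboptimal balloon result, which may narrow any gap between occlusions and stenoses.
- **That the plan already holds the adjustment model.** The logistic regression is a search for risk factors for recurrence with no named covariates. Covariates selected from the data could not be reused for the primary interval, and an odds ratio would not match a 10-point margin.
- **That randomisation is simple.** The article does not mention strata or blocks, but a condensed article may omit them.
- **That chance imbalance biases the verdict.** Its contribution is already within the sampling error of the crude interval. Adjustment removes the shift in the particular trial; it does not correct an invalid method.

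**Conclusion.** The point holds as a modest improvement in efficiency. The article fixes an unadjusted primary interval, says that patient and lesion characteristics matter for patency, and has two plausible factors known before allocation.

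At 120 evaluable patients per group and the article's 90 % and 88 %, the gain is about 0 to 4 points of power, from 50.9 % to at most about 55 %, for assumed R² between 0 and 0.10. The half-width falls from 7.91 to no less than 7.51 points. The range rests entirely on the assumed R². The choice of lesion type and limb status is a judgement, because the Discussion names neither as a predictor.

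A reader might infer that adjustment would rescue the power. It would not: the shortfall comes from the sample-size calculation and must be dealt with there.

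**What to change.** Before outcomes are examined (the article describes the trial as still recruiting), amend the Statistical analysis section to state that:

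- the primary 95 % CI is for the marginal (standardised) risk difference in 12-month patency, from a logistic model with stent group, lesion type (occlusion or stenosis) and limb status (claudication or critical limb ischemia);
- its lower limit is compared with the unchanged -10-point margin, with the same estimator in the intention-to-treat and per-protocol sets;
- the variance method is named, for example the delta method or the bootstrap;
- if the model does not converge, a Mantel-Haenszel stratified risk difference is used;
- the crude difference is reported as a sensitivity analysis;
- no further covariates enter, given about 26 expected failures.

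The estimand, the margin and patient numbers do not change, and both covariates follow from eligibility and pre-allocation assessment. The cost is a short paragraph of wording, slightly more analysis work, and possibly software beyond SPSS 20.0, which the article names for all analysis. If the two factors prove weakly prognostic, the return is close to nil.

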### Randomization and interventions

Prior to the endovascular intervention, informed consent (see Additional file 2) will be obtained from all participants by investigators. Aspirin and clopidogrel will be administered at least 12 hours before the procedure. Prior to the intervention, 70 to 100 units/kg of unfractionated heparin will be administered. Endovascular interventions will be carried out percutaneously, by placing a 6–8Fr sheath at the femoral artery via an antegrade approach or a contralateral crossover technique. In selected cases, a retrograde approach (from the distal superficial femoral artery (SFA), popliteal artery, or pedal arteries) and/or brachial approach will be allowed. Diagnostic angiography will be performed in two different views at least 30 to 45° apart to evaluate the structure of the target lesion. Femoropopliteal and tibial arteries will be visually checked for the presence of distal lesions. To document the precise location of the lesion and the site of the intervention, we will recommend the use of a ruler. In cases of total occlusion, both intraluminal and subintimal methods of recanalization will be allowed. During the procedure, the use of other special devices will be allowed; for example reentry devices OUTBACK™ catheters (Cordis Corp., Miami Lakes, FL, USA) and Offroad catheters (Boston Scientific, Natick, MA, USA), chronic total occlusion (CTO) devices Frontrunner (Cordis Corp., Miami Lakes, FL, USA) and Truepath (Boston Scientific, Natick, MA, USA), and atherectomy devices such as SilverHawk™ and TurboHawk™ (Covidien, Plymouth, MN, USA). After the successful passage of the guidewire, predilation of the target lesion with an optimally sized balloon will be performed prior to stent implantation. Recommended minimal balloon dilation time is 120 seconds. Then, if there is a residual pressure gradient of ≥10 mmHg, residual stenosis of ≥30 %, or flow-limiting dissection, the balloon angioplasty results will be considered as suboptimal results. Subsequently, web-based randomization for stent selection will be performed. Patients will be randomly allocated to one of two groups, the balloon-expandable or self-expandable stent group, according to the stent deployment method. Random allocation of the patients will be performed via a web-based computerized program separately managed at the Cardiovascular Intervention Research Institute (CIRI), Korea University Guro Hospital, Seoul, Republic of Korea. Patients will be randomized in a 1:1 manner according to two different stents (SCUBA™ versus COMPLETE-SE™). The stents will be implanted to extend 10 mm proximally and distally from the margins of the target lesion with luminal narrowing of ≥50 %. A proper stent size will be selected after review of the baseline angiography results. If the stent is randomized to the COMPLETE-SE™, a stent with a diameter 1 to 2 mm larger than that of the true vessel lumen will be selected. However, if the stent is randomized to the SCUBA™ stent, a stent of equal size to the reference vessel diameter will be selected to prevent iliac artery injury. Spot stenting or full lesion coverage will be decided at the physician’s discretion. When multiple stents are required, the margins of the stents should be overlapped by at least 10 mm. Adjuvant postdilation after the stenting will be performed strictly within the stented segment, with up to 10 % oversizing of the postdilation balloon.

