
The self-expandable COMPLETE-SE™ stent has three distinct crown configurations, and an alternating connection pattern minimizes crown-to-crown interaction and provides optimal flexibility, foreshortening, and lesion coverage for each stent size. The triaxial deployment design includes an inner shaft, a retractable sheath, and a stabilizing sheath, which reduces friction and allows the retractable sheath to move back freely. This decreases the amount of force required to deploy the stent, making deployment easy and accurate. Diameter and length of self-expandable COMPLETE-SE™ stents are 5–10 mm and 20, 40, 60, 80, 100, 120, and 150 mm, respectively. Balloon-expandable SCUBA stents are composed of thin cobalt-chromium struts, unlike other stainless steel stents, and have a closed-cell design for tight scaffolding and appropriate radial strength in iliac lesions. Diameter and length of balloon-expandable SCUBA™ stents are 6–10 mm and 20, 30, 40, and 60 mm, respectively. The entire stent size (the COMPLETE-SE™ and SCUBA™ stent) is now 6-Fr sheath compatible. We will use either a 0.035” or 0.018” wire system and implant either a SCUBA™ or COMPLETE-SE™ stent. All ipsilateral femoropopliteal arterial lesions should be treated with angioplasty and/or stenting concomitantly and residual stenosis should be less than 50 %. Treatment of tibioperoneal lesions is recommended only in cases of CLI. There should exist at least one patent (<50 % stenosis) tibioperoneal run-off vessel with good antegrade flow. A final angiography will be performed after the intervention in both groups, with the use of the same angles and magnifications used at the baseline angiograms. Simultaneously, reference vessel diameter (RVD), minimal luminal diameter (MLD), percent diameter stenosis, and acute gain should be measured. The RVD will be obtained from averaging 5-mm segments proximal and distal to the lesion. Technical success will be defined as successful access, deployment of the stent, and less than 30 % diameter residual stenosis after the revascularization. For postprocedural medication, aspirin 100 mg and clopidogrel 75 mg will be administered once daily for at least 12 months. Cilostazol would be permitted as the third antiplatelet at the physician’s discretion. After enrollment and index procedure, clinical follow-up will be planned at 1, 6, and 12 months to evaluate clinical outcomes and ankle-brachial index (ABI) score. In addition, a follow-up catheter angiography, CT angiography, or duplex ultrasound will be recommended to all patients at 12 months, according to local clinical practice. The investigators will be urged to follow up on patients, either by office visits or by telephone contacts, as necessary. Patient adherence to the study drug and side effects will be checked and monitored at every outpatient visit. The decision of drug discontinuation will be discussed and checked at the physician’s recommendation.

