### Outcome measures

The primary end point of this study is the patency rate (stenosis of at least 50 % of the luminal diameter) on catheter or CT angiography or <2.5 of peak systolic velocity ratio (PSVR; peak systolic velocity within the area of stenosis divided by peak systolic velocity in a normal adjacent proximal artery segment) in the treated segment at 12 months after the intervention.

The secondary end points are as follows: (1) geographic miss rate (mild, moderate, severe); geographic miss refers to stent deployment to any area of the vessel that was intended to be treated with the stent but was not covered, or protrusion due to stent jumping, and/or elongation. Geographic miss rate is classified as 5–15 mm (mild), 15–25 mm (moderate), >25 mm (severe), or additional stent deployment over the stent deployment area that was not covered, or protrusion from the intended stent deployment area; (2) incidence of stent fracture; (3) limb salvage rate free of above-the-ankle amputation; (4) sustained clinical improvement rate at 12-month follow-up; (5) repeated target lesion revascularization (TLR) rate; (6) repeated target extremity revascularization (TER) rate; (7) total reocclusion rate; (8) comparison of angiographic variables including late loss and binary restenosis rate; (9) ABI at 12 months; (10) the rate of major adverse cardiovascular event (MACE), defined as composite of all-cause death, myocardial infarction, repeat percutaneous coronary intervention (PCI), and stroke at 12 months.

The detailed definitions are summarized in the Appendix.

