- Sustained clinical improvement rate [29, 30] defined as persistent ABI value ≥0.15 and persistent improvement of ≥1 class according to Rutherford throughout follow-up when compared with baseline without the need for repeat TLR in surviving patients. Late loss: defined as a change in MLD from final angiogram to follow-up
- Major adverse cardiac events (MACE): defined as composite of all-cause death, myocardial infarction, cerebrovascular stroke, and target lesion revascularization

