### 2. Immediate outcomes

- Acute lesion success: defined as a residual stenosis of ≤30 % without flow-limiting dissection in the worst angiographic view
- Definition of suboptimal result: residual pressure gradient of >15 mmHg, residual stenosis of >30 %, or flow-limiting dissection
- Acute hemodynamic success: defined as a ≥0.15 improvement in the ankle-brachial index from preprocedure to immediately postprocedure (discharge)
- Clinical success: defined as an improvement of baseline symptoms by at least one Rutherford category that was sustained throughout follow-up with no additional intervention

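### The 12-month ABI comparison uses an unadjusted t test although a pre-randomization ABI is already collected, so precision is given away

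*Protocol article*

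**What the plan says.** The Outcome measures section lists "ABI at 12 months" as secondary end point (9). The Statistical analysis section fixes the test in two places.

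- General rule: "Continuous variables will be expressed as mean ± standard deviation, and for continuous variables, comparisons between groups will use the Student" t test.
- Secondary end points: "we will summarize with descriptive statistics and compare between treatment groups using the Student" t test, the chi-square test or Fisher's exact test.

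No covariate is named for any of these comparisons. The only regression planned is a logistic model for risk factors for restenosis or occlusion, which does not cover ABI.

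The protocol also relies on an ABI taken before the procedure. Appendix section 2 defines acute hemodynamic success as a gain of at least 0.15, namely an "improvement in the ankle-brachial index from preprocedure to immediately postprocedure (discharge"). Appendix section 1 defines sustained clinical improvement by an ABI criterion together with "persistent improvement of ≥1 class according to Rutherford throughout follow-up when compared with baseline". Follow-up ABI is scheduled as well: "clinical follow-up will be planned at 1, 6, and 12 months to evaluate clinical outcomes and ankle-brachial index (ABI) score".

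Randomization takes place during the procedure, once balloon angioplasty has given a suboptimal result: "Subsequently, web-based randomization for stent selection will be performed".

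**The concern.** When a continuous outcome is also measured before randomization, a t test on the follow-up value alone leaves in the error term the part of the outcome variance that baseline could explain. The confidence interval is then wider than the collected data allow. A chance baseline difference between the groups also shifts the observed 12-month difference, by the imbalance times the slope of 12-month on baseline ABI.

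There is reason to expect baseline ABI to carry some information here. Enrolment covers Rutherford 2 to 6 and lesions from more than 50 % stenosis to occlusion. Tibioperoneal treatment is recommended only in CLI, and femoropopliteal residual stenosis is accepted up to a limit. Some distal disease present at baseline can therefore persist at 12 months and lower both readings. The article describes 1:1 allocation and names no stratification factor, so nothing described in the design limits imbalance in baseline ABI.

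At stake is the precision of one secondary comparison. The primary patency analysis is not involved.

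**Working it through.** **Plan's own figure.** There is none to reproduce. The protocol gives no SD, correlation, target difference or power for ABI.

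**Inputs**

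- Method: unadjusted t test (Statistical analysis).
- Covariate: pre-procedure ABI (Appendix section 2). It precedes randomization (Randomization and interventions), so the allocated stent cannot affect it.
- Reference size: 120 per group (Sample size calculation). This figure belongs to the patency end point and is used here only as a yardstick.
- Significance level: P < 0.05, taken as two-sided.
- r, the correlation of pre-procedure with 12-month ABI: not given. Assumed 0.2 to 0.7.

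**Formulas.** With outcome SD σ and n per group:

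- t test: variance of the difference = 2σ²/n
- ANCOVA: variance ≈ 2σ²(1 − r²)/n
- Variance ratio = 1 − r²; CI width ratio = √(1 − r²); equivalent size = n/(1 − r²)

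At 120 per group the t test has 80 % power at a difference of (1.96 + 0.84) × √(2/120) = 0.362 SD. At that same difference, ANCOVA power is Φ(2.80/√(1 − r²) − 1.96).

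**Results at 120 per group**

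| Assumed r | Variance ratio | CI narrower by | Equivalent per group | ANCOVA power |
|---|---|---|---|---|
| 0.2 | 0.96 | 2.0 % | 125 | 81.6 % |
| 0.3 | 0.91 | 4.6 % | 132 | 83.6 % |
| 0.4 | 0.84 | 8.3 % | 143 | 86.4 % |
| 0.5 | 0.75 | 13.4 % | 160 | 89.9 % |
| 0.6 | 0.64 | 20.0 % | 188 | 93.8 % |
| 0.7 | 0.51 | 28.6 % | 235 | 97.5 % |

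Worked row, r = 0.5: 1 − 0.25 = 0.75; √0.75 = 0.866; 120/0.75 = 160; 2.80/0.866 − 1.96 = 1.275, and Φ(1.275) = 0.899.

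**Dependence on n.** The variance ratio does not depend on n, apart from one degree of freedom. With 112 evaluable per group (the abstract's 280 patients, halved, less 20 %), r = 0.5 gives 112/0.75 ≈ 149.

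**Chance imbalance.** The standard error of the baseline difference is √(2/120) = 0.129 baseline SD. An imbalance at the edge of its 95 % range is 1.96 × 0.129 = 0.253 SD. In SD units the slope equals r, so the unadjusted 12-month difference would shift by 0.253r SD: 0.08 SD at r = 0.3, 0.13 at 0.5 and 0.18 at 0.7.

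**A separate matter.** The 120 itself does not follow from the stated patency inputs: (1.96 + 0.84)² × (0.90 × 0.10 + 0.88 × 0.12)/0.08² = 7.85 × 0.1956/0.0064 ≈ 240 per group. This does not change the variance ratios above.

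**The case against.** **The t test is valid.** Under 1:1 randomization it is unbiased, and its interval already allows, on average, for chance imbalance. ABI is ninth of ten secondary end points, with no hypothesis, margin or alpha of its own. All of this stands. It limits the point to efficiency and keeps it away from the primary conclusion.

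**The analysis sentence is generic, and covariates are usually left to a SAP.** This stands only in part. The protocol is not silent: it names the t test for continuous variables and for secondary end points.

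**Wide baseline spread does not by itself show a loss.** The t test's error variance is that of the 12-month value, and baseline matters only through its correlation with that value. This is right, and it is why every figure above is expressed through r.

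**r may be low.** The procedure is meant to relieve the iliac obstruction, femoropopliteal lesions are to be treated at the same session, and at least one patent run-off vessel is required. Much of what sets baseline ABI is therefore altered on the day. This is the strongest objection. If r is 0.2, the interval narrows by only 2.0 %, and nothing in the protocol supports a value as high as 0.7.

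**The equivalent sizes are borrowed.** The 120 comes from the patency calculation, and the number of patients with both ABI readings is unknown. This is true of the equivalent sizes, but the variance ratio does not rest on it.

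**Baseline ABI is not wholly unused.** It enters acute hemodynamic success and, it appears, sustained clinical improvement. Both are dichotomies and do not replace an adjusted comparison of 12-month ABI.

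**Conclusion.** The concern holds. The protocol prescribes an unadjusted t test for 12-month ABI although it needs a pre-randomization ABI for other definitions, and no other text adjusts the comparison. The cost is lost precision; the planned test remains valid.

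The size rests on an r the protocol does not give. The variance that baseline adjustment would remove is 9 % at r = 0.3, 25 % at 0.5 and 49 % at 0.7. It is small below about 0.3 and material from about 0.5. That the t test is prescribed and the covariate available is certain from the text; the size of the gain is not. Because adjustment uses one extra parameter and data the trial already needs, the change is worth making even if r proves modest.

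**What to change.** In the Statistical analysis section, state that 12-month ABI will be compared by a linear model (ANCOVA) with stent group and the pre-procedure ABI of the index limb as covariate, reporting the adjusted difference with its 95 % CI. The t test can stay as a supportive analysis.

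The sentence should name the pre-procedure value explicitly. The discharge ABI must not be the covariate, because it is measured after stenting and may already reflect the allocated device.

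The cost is one sentence, with no new visits, measurements or patients, provided pre-procedure ABI is recorded for all patients, as the definition of acute hemodynamic success requires. The article describes the trial as still recruiting. The change should be fixed before any 12-month comparison by group, so that the choice between adjusted and unadjusted results is not made after seeing them.
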